#### Prospective recruitment

Potential participants will be informed about the study by their obstetric healthcare professional when admitted to the hospital. First, the healthcare professionals will verify the inclusion and exclusion criteria (table 1), after which the women are added to the study using an encryption key. These women are part of the cohort study and receive standard care consisting of conventional intermittent CTG monitoring. A part of these women will be randomly sampled. This random sampling is conducted by the research team using a secure algorithm embedded in Research Manager (ISO 27001 certified). They will be offered the new treatment: continuous eCTG monitoring using the NFMS (figure 2). The women will either be part of the cohort study, thus receiving standard care consisting of conventional intermittent CTG monitoring, or they will be sampled for continuous eCTG monitoring using the NFMS. Appropriate explanation and written study information will be provided hereafter by the healthcare professional, and they will ask the researchers for further counselling. Non-sampled women will only receive information regarding the collection of their data in the cohort study. Sampled women will be informed about receiving continuous eCTG monitoring. A researcher will complete the informed consent (IC) procedure, including collecting written consent (for an example of the participant consent form, see online supplemental file 1). When the women do not wish to participate in the study, they will be excluded, their encrypted information will be obliterated and the exclusion will be anonymously documented. Once women are included, they are given the appropriate monitoring method. Five NFMS devices are available at the OHC of Máxima MC. When no NFMS device is available within 24 hours after sampling and inclusion, the sampled women will receive standard treatment within the study. For continuous monitoring, trained nursing staff will oversee device placement and signal quality checks during routine care. CTG traces are continuously displayed on a central monitoring system, where deviations from normal patterns trigger automated alarms to alert clinical staff. In addition, CTG traces are systematically assessed by physicians at least four times per 24 hours at predefined intervals, partly retrospectively, and more frequently if clinically indicated. These assessments follow a standard operating procedure (SOP) to ensure consistency and clinical relevance. If the eCTG recording does not provide sufficient signal quality for reliable monitoring, we will report this and, if needed, can be switched to standard CTG monitoring. This decision will be made on the clinical judgement of the attending gynaecologist. No literature was available on an acceptable signal loss threshold. The International Federation of Gynaecology and Obstetrics Guidelines advises switching monitoring methods in intrapartum monitoring when a signal loss threshold of 20% is reached.^35^ Based on this, a standardised protocol for switching to conventional CTG will be implemented when signal loss exceeds 20%, or when clinical judgement deems the eCTG trace insufficient for reliable interpretation. This protocol will be documented and monitored throughout the study. Women who decline to be part of the cohort will receive standard care: conventional CTG monitoring without data collection for research. All prospectively included women will receive a digital invitation to two digital surveys. Women are asked to fill in the first survey about their experience with the received monitoring method—EQ5D5L questionnaire^36^—on the first day after admission, and the second survey about their experience—D-QUEST^37^—on the last day of admission. Although the patient satisfaction surveys are administered at admission and discharge, all participants are followed up until (at least) 4 weeks postpartum. During this period, patients have the opportunity to share additional reflections or concerns with their care team, which may provide further qualitative insights into their experience with the monitoring method.

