### Statistical analysis

For the primary and secondary outcomes, based on the demographics, characteristics of the women and their baseline outcomes, a propensity score will be created. This will be used to correct for possible selection bias that may occur due to (1) the group of women who are offered eCTG but receive CTG (either by choice or circumstances) or (2) the retrospective and prospective nature of the study. Thus, a per-protocol analysis with propensity score adjustment will be considered. The propensity score models will include maternal characteristics (eg, age, BMI, parity, ethnicity), foetal indicators (eg, gestational age, foetal growth restriction, Doppler abnormalities) and care-related variables (eg, indication for admission, medication use, duration of hospitalisation). These covariates were selected based on clinical relevance and availability across both cohorts. For categorical outcomes, a logistic regression analysis will be applied to estimate the treatment effect corrected for the propensity score. For numerical outcome values, a general linear model will be applied with an appropriate probability distribution link function and the sandwich estimator to estimate a treatment effect corrected for the propensity score. For time-to-event outcome, a Cox proportional hazards model will be used with a sandwich estimator to estimate a treatment effect corrected for the propensity score. For the data gathered from the questionnaires, standard statistical tests will be used (χ^2^, t-test, Mann-Whitney tests) to determine a difference between the two treatment groups. A propensity score approach will be applied as well if large imbalances between characteristics are present between CTG and eCTG participants. Several sensitivity analyses are being anticipated. The combined endpoint will be analysed as separate end-points. Several subgroup analyses are investigated (eg, obesity). A p value of <0.05 is considered statistically significant unless otherwise specified. When possible, 95% CIs will be calculated for the reported measures of effect. Missing data will be evaluated and reported. Limited missing data is expected, and if missingness is less than 5%, list-wise deletion will be used. Otherwise, multiple imputation (eg, predictive mean matching) will be used. The imputation will be repeated at least 10 times and Rubin’s rule will be used to combine estimates and standard errors from the imputed data.

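### The only EQ-5D-5L is timed from admission, at or near the start of eCTG, so it mostly reflects health near entry and is poorly suited to serve as a survey of experience with the monitoring method

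*Protocol article*

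**What the plan says.** All of the following is in the protocol article.

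- **Number of surveys** (Prospective recruitment): "All prospectively included women will receive a digital invitation to two digital surveys".
- **First survey** (same section): "Women are asked to fill in the first survey about their experience with the received monitoring method—EQ5D5L questionnaire". Its timing, and the start of the second, read "on the first day after admission, and the second survey about their experience".
- **Second survey**: the D-QUEST, due "on the last day of admission". Further down, the pair is summed up with "Although the patient satisfaction surveys are administered at admission and discharge".
- **Start of monitoring** (same section): "Once women are included, they are given the appropriate monitoring method". Eligibility check, sampling, written information, counselling and consent come first. On device supply: "When no NFMS device is available within 24 hours after sampling and inclusion, the sampled women will receive standard treatment within the study".
- **Objective served** (Study objectives): patient satisfaction is one of several secondary objectives.
- **Analysis** (Statistical analysis): questionnaire data go to chi-squared, t or Mann-Whitney tests "to determine a difference between the two treatment groups". The next sentence adds a propensity score approach if there are large imbalances in characteristics. No baseline role is stated for the first survey.

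**The concern.** Two features of the first survey do not fit its stated purpose.

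The first is timing. The survey clock starts at admission, whereas the eCTG clock starts at inclusion plus any wait for one of the five devices. A woman can be asked about the method she received before she has received it, or after only a few hours of it.

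The second is the instrument. The EQ-5D-5L is a general health-status questionnaire, not a measure of experience with a monitor. That it is generic is common knowledge rather than something the article states, and the timing argument stands without it.

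Together these make the day-1 score mainly a description of how well the woman was near entry. If it is then tested between groups as an experience outcome, a difference may show only who ended up in each group, and no difference may show only that there was little exposure. Because the listed schedule gives the EQ-5D-5L once, there is no later value from which to judge whether about a day-round patch (at least 21 hours per 24, under Intervention) changes general health status during the stay.

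**Working it through.** The plan states no figure for this point, so the check is the survey schedule set against the start of monitoring, plus the size of the groups surveyed.

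**1. Exposure at the first survey**

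Hours on eCTG at the survey = max(0, S − L − W), where

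- S = hours from admission to completing the survey. The article says only the first day after admission, so 12, 24, 36 and 48 are assumed.
- L = hours from admission to inclusion. No limit is given; 0, 12 and 24 are assumed.
- W = hours from inclusion to receiving a device. The stated cut-off is 24; 0, 12 and 24 are used.

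| S | L | W = 0 | W = 12 | W = 24 |
|---|---|---|---|---|
| 12 | 0 | 12 | 0 | 0 |
| 12 | 12 | 0 | 0 | 0 |
| 12 | 24 | 0 | 0 | 0 |
| 24 | 0 | 24 | 12 | 0 |
| 24 | 12 | 12 | 0 | 0 |
| 24 | 24 | 0 | 0 | 0 |
| 36 | 0 | 36 | 24 | 12 |
| 36 | 12 | 24 | 12 | 0 |
| 36 | 24 | 12 | 0 | 0 |
| 48 | 0 | 48 | 36 | 24 |
| 48 | 12 | 36 | 24 | 12 |
| 48 | 24 | 24 | 12 | 0 |

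For example, with a survey at 24 hours, a 12-hour inclusion lag and a 12-hour device wait, 24 − 12 − 12 = 0 hours. With the same survey hour and no delay, 24 − 0 − 0 = 24 hours. The cells show what the schedule permits. They are not frequencies, because the article gives no distribution of lag or wait.

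**2. Who is compared**

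Only prospective women are surveyed, so the 1400 historical controls do not contribute. From Sample size:

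- sampled women who consent: 464 × 0.80 = 371.2 (article: 372)
- of these, on eCTG: 372 × 0.90 = 334.8 (article: 335)
- sampled women who decline eCTG: 372 − 335 = 37
- non-sampled women who consent: 47 × 0.80 = 37.6 (article: 37)

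The prospective CTG group is therefore 37 + 37 = 74, of whom 37/74 = 50% declined eCTG. The expected comparison is 335 with 74 before any survey non-response, and half of the smaller group is there by its own choice. Sampled women who get no device in time would also be on CTG; the sample-size flow does not count them separately.

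**3. Whether a later value exists**

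Two surveys are listed, one of each instrument. The D-QUEST at discharge is a different instrument, so neither a change in EQ-5D-5L nor a last-day EQ-5D-5L adjusted for day 1 can be calculated from the listed schedule.

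**The case against.** The strongest reply has five parts.

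- **Exposure need not be small.** No survey hour is given, and monitoring normally starts once a woman is included. The 24 hours is the limit after which a woman without a device receives standard treatment, not a typical wait. This stands. A reader might infer that the survey cannot show any effect, or that many eCTG women will have had almost none of the method. The article does not support either: promptly fitted women could have a day or more, and nothing gives the share with little or none.
- **The analysis has a safeguard.** Propensity adjustment is foreseen when imbalances are large. This stands in part. It is conditional, and it cannot supply exposure time that had not accrued.
- **Experience is measured after exposure.** The D-QUEST is given on the last day, and skin irritation is recorded as an adverse outcome (Ethics and risk assessment). This stands. A reader might infer that the burden of the patch is never measured, or that the satisfaction objective fails; neither follows. The content of the D-QUEST is not shown, so it cannot be said to miss discomfort.
- **This is a condensed article.** The full protocol or SAP may treat the day-1 score as baseline or list a repeat. The first is possible and would settle the analysis. A repeat is a matter of data collection, though: an SAP cannot create a measurement that was not taken, and the article itself states instrument, timing and purpose. If the full protocol has a repeat, the article needs correcting.
- **It is a small matter.** It concerns one of two patient questionnaires under one secondary objective. That is right about scope, but the remedy is correspondingly cheap.

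**Conclusion.** The point holds as a mismatch between the first survey's label and what its instrument and timing can deliver. The EQ-5D-5L is presented as a survey of experience with the received method but is taken at or near the start of exposure. Under the assumed timings, exposure runs from 0 to 48 hours, and is 0 to 24 hours if the form is completed 24 hours after admission. The score will mostly reflect health near entry and is poorly suited to show an effect of method. With no repeat listed, no later EQ-5D-5L value can make up for this.

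The between-group test adds a risk of misreading, since the expected CTG side is about 74 women, half of them decliners, with only conditional adjustment. That figure rests on the article's own acceptance rates.

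The consequence is limited. The primary outcome, its sample size and its analysis are untouched, and the D-QUEST still gives a post-exposure comparison for satisfaction. The change is worth making because it is cheap and because the missing second score cannot be recovered after discharge.

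**What to change.** 1. Describe the day-1 EQ-5D-5L as a baseline health measure, and do not test it between groups as an experience or satisfaction outcome.
2. Add the same EQ-5D-5L to the digital survey already sent on the last day of admission. Compare the last-day score between groups, adjusted for the day-1 score.
3. Base the patient satisfaction comparison on the D-QUEST.
4. Record when monitoring started and when the first survey was completed, so that hours on eCTG at day 1 are known. For women already on eCTG by then the day-1 score is not strictly pre-exposure, and the report should say how many there were.

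Cost: a wording change in the survey and analysis text, and one short extra questionnaire per woman at discharge. Women already discharged will lack the second score, so the earlier the change is made, the fewer are lost to this comparison. Adjusting for the day-1 score deals with differences in health near entry. It does not remove every difference between women who accept and women who decline eCTG, so the planned propensity approach remains relevant to the questionnaires.

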
**Figure 2 F2:**
[figure not shown]
The Nemo Foetal Monitoring System (NFMS) consists of three components: base, link and patch (source: user manual NFMS).

Additionally, for the development and validation of a mathematical model regarding the automated detection of foetal movement, the first 200 consecutive women monitored with NFMS will receive a parallel 45 min ultrasound recording extended with a six-channel accelerometric measurement. The ultrasound will be annotated in real-time for foetal movement and will be performed within 4 days following admittance.

Finally, if patients are admitted to the OHC repeatedly, they stay in the same monitoring group, not allowing cross-over with the other group. Caregivers will receive a validated digital survey designed by Brown *et al*^38^ at the start of the study and after 1 year to evaluate their satisfaction regarding the monitoring methods.

#### Retrospective recruitment

In order to strengthen the comparison of the two groups (continuous eCTG monitoring and conventional intermittent CTG monitoring), additional data from women who received standard treatment (conventional intermittent CTG monitoring) in Máxima MC Veldhoven, the Netherlands in 2014–2019 will be collected retrospectively. Data will be derived from electronic patient records (EPRs).

#### Data collection

All required demographic and medical information will be obtained from the EPR at the Máxima MC or the referring hospital, when the patient has been transferred to or from this hospital before or after their admission to the OHC. This includes maternal and perinatal information. For the mother: age, ethnicity, BMI, obstetric history, general medical history, medication use, intoxications, information about the course of pregnancy, complications during pregnancy, delivery and (until 6 weeks) postpartum, For the fetus/neonate: ultrasound results such as foetal biometry, structural abnormalities or Doppler measurements, gestational age at delivery, gender, birth weight, admission to neonatal ward and the reason for admission, Apgar scores, pH and base excess in umbilical artery and vein, mortality, morbidity, general information on neonatal health in the first 4 weeks postpartum. Research Manager (ISO 27001 certified) is used to store patient data.

### Intervention

Sampled women will receive continuous eCTG monitoring (when accepted), using the NFMS. The system is CE (Conformité Européenne) -licensed and already in use as standard care in several hospitals throughout Europe. The NFMS consists of a base, link and abdominal patch (figure 2). Corresponding to the manufacturer’s instructions, the electrode patch will be applied by trained personnel and employed inside the uterus boundaries. Before application of the patch, the abdominal skin must be washed thoroughly with water and soap and subsequently gently abraded with medical abrasive paper. This procedure is necessary to achieve low skin impedance and ensure good electrical conduction of the foetal heart signal.^39^ Every recording will continue 24/7, with a minimum of 21 hours per 24 hours.

### Sample size

A total of 1911 patients (comprised of 511 prospectively included women and 1400 historical controls) would be sufficient to evaluate the primary objective. Incidence of the composite outcome is based on numbers of perinatal morbidity and mortality of MMC from 2019, combined with a literature-based estimation of the simultaneous occurrence of the perinatal comorbidities and mortality.^40^,^43^ Due to the unknown effect of COVID on perinatal and maternal outcomes,^44^ numbers from MMC of 2020–2021 are not included in the sample size calculation. This resulted in a rounded estimated composite outcome of 17%. Based on clinical experience, an effect size of 6% is expected. To detect this effect size with a power of 80% and a type I error of 5%, a group of 511 women will be invited for the prospective cohort. Of these 511 women, 464 women (90.8%) will be in the sampled study arm and 47 women (9.2%) in the non-sampled study arm. Based on clinical experience, an estimation of 80% acceptance rate for data collection in the sampled and non-sampled group was made (resulting in 372 women and 37 women respectively). Among the 372 women who agreed to data collection in the sampled group, it is expected that 90% will accept and receive eCTG monitoring (335 women) and 10% (37 women) will decline eCTG monitoring and therefore receive CTG monitoring. All 37 women in the non-sampled group will receive standard monitoring. For the retrospective cohort, a total of 1400 participants will be included (figure 3). No dropout rate is calculated, due to continuation of the study and sampling until the requested sample size (of both groups) is reached.

**Figure 3 F3:**
[figure not shown]
Flowchart of sample size calculation including estimation of informed consent (IC) and eCTG acceptance rates. CTG, cardiotocography; eCTG, electrophysiological cardiotocography.

### Statistical analysis

For the primary and secondary outcomes, based on the demographics, characteristics of the women and their baseline outcomes, a propensity score will be created. This will be used to correct for possible selection bias that may occur due to (1) the group of women who are offered eCTG but receive CTG (either by choice or circumstances) or (2) the retrospective and prospective nature of the study. Thus, a per-protocol analysis with propensity score adjustment will be considered. The propensity score models will include maternal characteristics (eg, age, BMI, parity, ethnicity), foetal indicators (eg, gestational age, foetal growth restriction, Doppler abnormalities) and care-related variables (eg, indication for admission, medication use, duration of hospitalisation). These covariates were selected based on clinical relevance and availability across both cohorts. For categorical outcomes, a logistic regression analysis will be applied to estimate the treatment effect corrected for the propensity score. For numerical outcome values, a general linear model will be applied with an appropriate probability distribution link function and the sandwich estimator to estimate a treatment effect corrected for the propensity score. For time-to-event outcome, a Cox proportional hazards model will be used with a sandwich estimator to estimate a treatment effect corrected for the propensity score. For the data gathered from the questionnaires, standard statistical tests will be used (χ^2^, t-test, Mann-Whitney tests) to determine a difference between the two treatment groups. A propensity score approach will be applied as well if large imbalances between characteristics are present between CTG and eCTG participants. Several sensitivity analyses are being anticipated. The combined endpoint will be analysed as separate end-points. Several subgroup analyses are investigated (eg, obesity). A p value of <0.05 is considered statistically significant unless otherwise specified. When possible, 95% CIs will be calculated for the reported measures of effect. Missing data will be evaluated and reported. Limited missing data is expected, and if missingness is less than 5%, list-wise deletion will be used. Otherwise, multiple imputation (eg, predictive mean matching) will be used. The imputation will be repeated at least 10 times and Rubin’s rule will be used to combine estimates and standard errors from the imputed data.

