### Study objectives

The primary objective of the study is to evaluate the effect of continuous antepartum eCTG monitoring on severe perinatal morbidity and mortality, by comparing with conventional intermittent CTG monitoring. The objectives are investigated in preterm fetuses (GA 23–32 weeks) whose mothers are admitted to the OHC. The primary study outcome is a composite outcome consisting of (1) Perinatal mortality, defined by the WHO as: deaths that occur after a gestational age of ≥22 weeks or, if unknown >500 gram, until 28 days after birth^20^ and (2) Major neonatal morbidity assessed at the time point when the neonate is discharged from the hospital.^21^ Major neonatal morbidity is defined as either: intraventricular haemorrhage (IVH) grade three or more,^22 23^ periventricular leukomalacia (PVL) grade two or more,^24 25^ moderate or severe bronchopulmonary dysplasia (BPD),^26^,^28^ necrotising enterocolitis (NEC) grade two or more,^29 30^ or retinopathy of prematurity (ROP) necessitating laser therapy.^31^ Secondary study objectives are the effect of continuous antepartum eCTG compared with conventional intermittent CTG monitoring on maternal mortality, neonatal morbidity, satisfaction for both patient and caregiver, duration of pregnancy, the need to switch between monitoring methods (either from eCTG to CTG or vice versa), timing and number of obstetric interventions, duration of admission at the OHC and admission and duration of admission at the neonatal intensive care unit. Demographics will be obtained from the electronic patient file. The secondary outcomes are defined as follows: maternal mortality as defined by the WHO^32^: any death from any cause related to or aggravated by pregnancy or its management (excluding accidental or incidental causes) during pregnancy and childbirth or within 42 days of termination of pregnancy, irrespective of the duration and the site of the pregnancy. Neonatal morbidity, excluding major neonatal morbidity described as primary outcome, is defined as: Any health condition attributed to and/or aggravated by birth, assessed at the time point when the neonate is discharged from the hospital^21^ or—if discharged within 4 weeks after birth—at 4 weeks after birth, that has negative outcomes to the neonatal well-being (ie, IVH grade 1–2, PVL grade 1, mild BPD, NEC grade 1, ROP (any grade)) not necessitating laser therapy, hypoxic ischaemic encephalopathy, neonatal seizures, neonatal sepsis (culture proven), need for intubation on the delivery room, mechanical ventilation within the first 72 hours after birth, antibiotics within the first 72 hours after birth, spontaneous intestinal perforation necessitating surgery, surfactant treatment, Apgar score <7 after 5 min, severe metabolic acidosis (pH <7.05 and base deficit ≥12 mmol/L). This definition of severe metabolic acidosis is set at pH <7.10 and base excess ≥12 mmol/L in cases with only an umbilical vein sample (one available blood gas sample or the pH difference between two samples below 0.03^33^). Next to the study objectives described above, the data that is gathered in this study will be used to develop and verify mathematical models that aim at the prediction of time to (premature) birth and at automated detection of foetal movements.

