## Discussion

The NIEM-O study investigates the effect of continuous antepartum eCTG monitoring compared with conventional intermittent CTG monitoring, in preterm hospitalised high-risk pregnancies, on perinatal and maternal outcome. Our hypothesis is that the novel monitoring technique (eCTG) and its continuous antepartum use may lead to earlier detection of foetal distress and may prevent unnecessary interventions. This might result in improved perinatal and maternal outcomes. It also provides more insight into preterm and continuous antepartum foetal monitoring. This will support consensus and recommendations regarding the interpretation of antepartum foetal monitoring for preterm fetuses.^45 46^ Similarly, limited knowledge exists regarding the utilisation and interpretation of continuous (electrophysiological) foetal monitoring (eCFM) for a prolonged period of time.^47^ The comprehensive nature of this study’s database renders it suitable for future research inquiries and as a reference database.

A similar large-scale clinical study (NIEM-II study) is currently being conducted in the term population, comparing the effect of eCTG with conventional CTG monitoring during labour on various perinatal and maternal outcomes.^48^ Both studies—this NIEM-O study and the NIEM-II study—employ the same CIRSS design, enabling efficient implementation and comparison of eCTG with standard monitoring in routine clinical care across different obstetric populations.

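### The propensity score includes duration of hospitalisation, which is known only after monitoring starts and largely coincides with a secondary outcome

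*Protocol article*

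**What the plan says.** The Statistical analysis section states: "For the primary and secondary outcomes, based on the demographics, characteristics of the women and their baseline outcomes, a propensity score will be created". It then lists what the propensity score models will include: maternal characteristics, foetal indicators and "care-related variables (eg, indication for admission, medication use, duration of hospitalisation". The selection rule is: "These covariates were selected based on clinical relevance and availability across both cohorts".

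Under Study objectives, the secondary objectives include "timing and number of obstetric interventions, duration of admission at the OHC", along with duration of pregnancy. Under Prospective recruitment, women are checked for eligibility on admission, sampled, asked for consent and then given their monitoring method. The Discussion gives the hypothesis for eCTG: "its continuous antepartum use may lead to earlier detection of foetal distress and may prevent unnecessary interventions".

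**The concern.** A propensity score is meant to make the groups comparable on what was true before treatment. Total duration of hospitalisation is known only when the stay ends, after monitoring has had its chance to act. It therefore does not fit the section's own description of a score built on characteristics and baseline values. The selection rule does not catch this, because it asks for relevance and availability and does not require a covariate to precede treatment.

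Two analyses are at stake. The first is length of OHC admission: a score that contains this duration makes the groups alike on the outcome before they are compared. The second is the primary composite. If eCTG changes when women are delivered or discharged, stay is a consequence of treatment. Adjusting for it can then remove part of the effect, or create a spurious association through unmeasured severity. The adjustment carries most of the weight in this design, because 1400 of the expected 1474 CTG women (95%) are historical.

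**Working it through.** **1. The plan's own figure.** The Sample size section gives a 17% event rate, a 6-point effect, 80% power and 5% type I error. It expects 335 women on eCTG, and CTG women 1400 + 37 + 37 = 1474. I take the test as two-sided and the effect as a reduction to 11%.

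- Pooled rate: (335 × 0.11 + 1474 × 0.17) / 1809 = 0.1589
- SE under no difference: √[0.1589 × 0.8411 × (1/335 + 1/1474)] = 0.02213
- SE under the alternative: √[0.11 × 0.89/335 + 0.17 × 0.83/1474] = 0.01970
- Power: Φ[(0.06 − 1.96 × 0.02213) / 0.01970] = Φ(0.844) = 80%

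The design figure reproduces. It is not in dispute, and the fix does not change it.

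**2. Length of admission.** Let T be treatment, X the baseline covariates, L the length of stay and e(X, L) the score. By the balancing property, L is independent of T given e(X, L). So the adjusted effect of T on L is zero whatever the truth, provided the L in the score is the L being analysed.

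A simulation of 335 v 1474 women (400 runs per scenario, one baseline confounder, score used as a regression covariate and as weights to the eCTG group) shows this on log stay:

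- Assumed truth −0.223 (20% shorter): baseline-only score −0.225; score with stay 0.000
- Assumed truth +0.223 (25% longer): baseline-only score about +0.224; score with stay 0.000

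If hospitalisation also counts independent days elsewhere (assumed mean 12 days), about 1.0 day of an assumed 3-day effect survives. The estimate is then attenuated but not abolished.

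**3. Primary outcome.** Risk differences in percentage points from the same simulation, by weighting. All effect sizes and causal structures are assumptions.

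| Assumed structure | Truth | Baseline-only score | Score with stay |
|---|---|---|---|
| Stay 20% shorter; sicker women stay longer and do worse | −6.1 | −6.2 | −4.7 |
| Stay 25% longer; same severity pattern | −6.1 | −6.2 | −7.8 |
| Stay 25% longer; longer stay itself protects | −5.5 | −5.6 | −3.4 |
| Stay 25% longer; sicker women stay shorter and do worse | −6.1 | −6.0 | −4.5 |
| Stay unchanged | −6.1 | −6.1 | −6.1 |
| Stay 25% longer; no primary effect; sicker women stay shorter and do worse | 0.0 | +0.1 | +1.6 |

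Against the baseline-only score, attenuation is 1 − 4.7/6.2 = 24%, 1 − 4.5/6.0 = 25% and 1 − 3.4/5.6 ≈ 40%. In the second row the effect is exaggerated by about a quarter (7.8/6.2).

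A different model lets stay run until delivery and makes the outcome depend on gestational age at birth (mean latency 14 days):

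- Stay 3 days longer: truth −5.7, estimate −4.3
- Stay 3 days shorter: truth −5.5, estimate −7.1

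So a shorter stay attenuates the effect in one model and exaggerates it in the other.

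**4. What attenuation would cost.** By the formula in step 1, shrinking 6 points by a quarter to 4.5 lowers power from 80% to about 53%. Shrinking it by 40% to 3.6 lowers power to about 35%.

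**The case against.** - **The two durations may differ.** One is hospitalisation, the other admission at the OHC. Transfers between hospitals (Data collection) and repeated admissions (Prospective recruitment) can separate them. This stands in part: a reader might infer that the stay effect must vanish entirely, but that needs the two to be identical. They overlap heavily, since the hospitalisation that qualifies a woman is to the OHC, so bias towards zero remains.
- **Primary bias is conditional.** A reader might infer that the primary result is certainly biased, or that benefit is overstated if eCTG shortens stay. The documents support neither. They give no effect of eCTG on stay, and the direction depends on the causal structure. Size does too: if half the women deliver after discharge, bias falls from about 1.4 to 0.5 points for a 21% longer stay.
- **Outcome-specific scores may be planned.** The section speaks of models in the plural, and the list is illustrative. But it names this variable as included, creates the score for primary and secondary outcomes, and makes no exception for length of admission.
- **Days before inclusion may be meant.** That would be harmless, but the text does not say so, and historical controls have no inclusion date unless one is defined.
- **Medication use may already be a baseline item.** That is possible, and nothing says that drugs started after inclusion enter the score. It needs a time limit stated, and is not shown to be an error.
- **Stay could correct for changes in practice since 2014–2019.** A variable that treatment can alter cannot separate calendar time from treatment.

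**Conclusion.** The point holds as wrong as written: a variable completed after monitoring begins is named in a score described as resting on baseline information, and it largely duplicates a secondary outcome.

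For length of admission, the estimate is driven towards zero. It reaches essentially zero if the two durations are the same, and this follows from how the score works, without any assumption about the effect of eCTG.

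For the primary composite, bias arises if eCTG changes length of stay, which the stated hypothesis makes plausible. Its size and direction cannot be known from the documents. The simulated range of 3.4 to 7.8 points against a truth of about 6 is illustrative only.

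**What to change.** In the Statistical analysis section, remove duration of hospitalisation from the propensity model, or define it as days already spent in hospital before time zero. Add the rule that only variables fixed before time zero enter the score, with medication limited to drugs in use or given before that point. Define time zero (for example, OHC admission) in the same way for prospective women and historical controls.

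The cost is a sentence or two in the protocol or SAP. The sample size does not change, and no extra patients or data are needed.
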